### Study approach

This study will be implemented following these stages;

#### Assess - document existing hand hygiene behaviour

In determining the barriers and opportunities for enhancing HCWs’ hand hygiene practices, this study component will involve collating and reviewing available published literature on hand hygiene provisions and drivers among HCWs in HCFs in Uganda and beyond. The literature review will be conducted with the help of a literature review guide. The findings from the literature review will guide the “build” (formative) research phase.

#### Build - formative phase

The formative research phase will address objectives 1 and 2 of the study, and the findings will inform the design and implementation of the intervention (mhealth and environmental cues on hand hygiene). The purpose of this formative phase is to understand the drivers of hand hygiene among HCWs. During this phase, we shall conduct key informants’ interviews (KIIs) and semi-structured interviews using developed guides. Multi-variation sampling will be conducted to select participants for the interviews and the sample sizes will be determined based on theoretical saturation in the data [32]. Structured observation checklists will be used to establish the status of HCF hygiene infrastructure and hand hygiene behaviour of HCWs.

#### Create - stakeholders’ workshops to develop and refine the intervention

A stakeholders’ workshop shall be conducted to share findings from the literature review, formative research and discuss the contextual mechanisms of designing and implementing the mhealth and environmental cues intervention. Stakeholders will give their ideas on how best the mhealth intervention should be designed and used to disseminate messages to HCWs. The choice of the environmental cues (colours or pictures to paint around hand hygiene stations, branding of mirrors etc) and the mhealth (mobile texting approach or use of social media such as Facebook or Whatsapp etc) for communicating behavioural change messages will depend on the guidance of the WASH stakeholders, subject area experts and reviewed literature. The stakeholders will include MWE, MOH, Kampala Capital City Authority (KCCA), Non-Government Organisation (NGOs), representatives from local authorities, District and HCFs’ IPCcommittees, WASH consultants as well as HCWs from different levels of HCFs in the GKMA.

During the stakeholders’ workshop, the World Café approach [33, 34] will be used, and 7–8 participants will sit around tables to internalize the findings from the formative research. Within the different groups, participants will use findings from the formative research to develop themes which will be used to develop insights, appealing stories that link the theme to the behaviour (hand hygiene among HCWs). The insights will be formulated to include: the behaviour to change; the character to influence; the motives to encourage the behaviour of that character as well as the direct or indirect reinforcement of social norms to encourage behaviour change. The insights from the different groups will be presented, and participants will choose the best 4–5 insights based on richness (how many of the formative research findings are captured by the insight), power (how strong the logic is in linking the insight to the target behaviour), plasticity (how likely the idea on which the insight is based could be changed by the intervention), novelty (is it a surprise and acceptable to the target population). Using “how might we questions”, participants will identify the campaign activities, tools and touch points that will enable HCWs to practice hand hygiene, change the settings, and create social norms.

The workshop will be used to develop and refine the intervention for implementation in the HCFs, using the workshop guide.

#### Delivery of the intervention

i.Intervention design

The study will be implemented through a CRT targeting HCWs working in maternity and children’s wards. The intervention will be implemented over a period of 4 months, through a partnership with WaterAid Uganda, MOH, KCCA, MWE as well as selected HCFs. The design of the study was guided by the checklist for standard protocol items recommended for international trials (SPIRIT), which is provided in Additional file 1.
ii.Trial interventions

In both the intervention and control HCFs, simple innovatively designed hand hygiene facilities (tapped plastic jerricans with a stand and basin) will be provided (where needed) in delivery rooms, post-natal wards, and children’s wards. Soap and ABHR will be provided at all hand hygiene stations. Additionally, ABHR will be provided at points of patient care and on medication trolleys. Hand hygiene demonstrations using the “glo germ” gel will be done in both study arms at the beginning of the study. The choice of the departments/wards for the interventions is based on the understanding that mothers and neonates face the greatest risk of infections related to poor WASH and IPC measures in HCFs [35], but these wards will also allow the research team to maximize the observations of hand hygiene opportunities while standing within a radius of about 5–10 m [36].

In the intervention HCFs, besides the provisions in the control group, two interventions, mhealth and environmental cues (nudges) that have been successful in enhancing adherence to treatment guidelines and enhancing hand-hygiene in school going children [19, 22] respectively will be used. The choice of the specific mhealth and nudges intervention, and the frequency of exposure to mhealth messages among the study participants will be determined in the insight workshop. The mhealth intervention messages will be designed with a focus on: benefits of hand hygiene; when to do hand hygiene; how to do hand hygiene and how to protect others. However, the messages will also have educational jokes and response prompts where HCWs with the highest number of responses will win hand hygiene supplies. This will be critical in enhancing participant retention and complete follow-up. The educational messages and jokes in the mhealth intervention will be guided by the results from the formative study.

The mhealth messages will be sent to study participants using either short message service (sms) or whataspp, depending on the decision of the stakeholders in the stakeholders’ workshop. In case stakeholders choose using the sms option, messages will be sent to participants using RapidSMS, which is a free and open-source framework for dynamic data collection, logistics coordination and communication. The service will enable a two-way communication between HCWs using basic SMS mobile phone technology. RapidSMS will be installed on a secure Linux server running Ubuntu 18.04.5 LTS with the following hardware specifications: (1) Intel Core i7-8700T 2.40 GHz processor with 16.0 GB of RAM, and (2) An MTCBA-GF4 modem attached via a serial interface. RapidSMS dependences that include Python and Django web framework will also be installed on the same machine. For compatibility, we shall install Python 3.7.3 and Django 2.2. For communication between the modem and RapidSMS, we shall install Kannel, which is a free and open source SMS gateway compatible with RapidSMS. With Kannel’s SMS Delivery Report functionality, we shall be able to track the status of messages sent to HCWs. We shall configure the system to automatically send mhealth messages to HCWs at specific weekly intervals. Our server will enable HCWs to respond to the messages sent by the system. SMS received by the system from HCWs will be toll free thus HCWs will not incur any costs when responding to mhealth messages. Responses from HCWs will be securely stored in MySQL database on the server; this will enable further analytics on the data. Authorized access to the data will be available via secure login into the system. The data will be available and downloadable in CSV format to enable further processing by third party statistical tools. The software can track message history and delivery, and this will be critical in understanding the proportion of HCWs receiving and responding to sms messages on a daily basis.
iii.Randomization and Trial arms

Using a list of level III and IV HCFs in the study districts [28], the project coordinator will use computer-generated random numbers to assign HCFs to the intervention and control arms. All HCWs from the same HCF will be allocated to the same group as the randomized HCF in which they are working. HCWs will be enrolled by research assistants (RAs) under the guidance of the principal investigator, and they will be masked off the intervention they are receiving.
iv.Masking/ blinding

The data analysts and the data collectors will be blinded to the group assignment. In order to achieve blinding for the data collection team, independent teams will collect data from either arm of the trial. In addition, data collectors will be trained separately.
xxii.Inclusion and exclusion criteria

The study will enrol participants working in the maternal and pediatric wards of selected HCFs, and Table 2 summarizes the inclusion and exclusion criteria.
vi.Intervention monitoring

**Table 2 Tab2:** Inclusion and exclusion criteria

Inclusion criteria	Exclusion criteria
• Age of 18 and above • Both male and female • Minimum of six months experience at the HCF. • HCWs with appointment letters to work at the selected HCF • Full-time staff at the selected HCF • Informed written consent to participate in the study	• All HCWs in maternal and children’s wards of selected HCFs, who will be on leave at the time of the baseline • All HCWs workers in maternal and children’s wards of selected HCFs, who will be so sick at the time of the baseline • Refusal to give informed written consent to participate in the study.

For quality delivery of the intervention and ensuring that results are acceptable to the different stakeholders, an intervention support team will be in place to provide technical guidance and support. The intervention support team or data monitoring committee (DMC) will be comprised of 6 members, with a representative from the Environmental Health Department at the MOH, KCCA Public Health department, MWE, NGOs, HCFs and private sector. The independent DMC will be chaired by a representative from the Environmental Health division at the MOH.

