Secondly, hand rinsates from HCWs participating in the CRT will be collected immediately after the hand hygiene observations during baseline and end-line. The samples (hand rinsates) will be collected by a team of trained environmental health officers. During sampling of hand rinsates, HCWs will put their hands, one at a time in Whirl-Pak bags containing distilled water. The HCWs will wash their hands by rubbing the inner hands for about 2 min and the enumerator massaging their hands from outside the whirl pak bag to remove any potential pathogens. Aseptic techniques will be used to collect duplicate samples from each of the study participants (HCWs) during baseline, midline and end-line. The samples will be stored in sterile plastic bottles and transported on ice to the laboratory for further analysis within 4 h. The hand rinsates will be analysed for *Escherichia coli (E.coli)*, to establish if there are differences in the levels of contamination on the hands of the HCWs before and after the intervention. During analysis, hand rinsates will be diluted using the ratios of 1:1, 1:10 and 1:100. The membrane filtration method (with Chromocult agar) will be used to concentrate samples, and incubation will be done at 37 °C for 24 h. Colonies of *E.coli* will be identified by their dark blue to violet colour, and they will be counted and recorded per 100 ml of sample.

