### Evaluation

We shall conduct process and outcome evaluations. The process evaluation will be conducted at the midline to understand how the intervention has been implemented. The process evaluation will seek to establish: whether the intervention is being implemented according to plan; whether the intervention is working or not; how many HCWs will be getting exposed to the touch points; how many HCWs will be responding to the mhealth intervention as well as the aspects of the intervention that participants will have liked. The baseline, midline and end-line evaluations will be conducted using a tool provided as Additional file 5.

To assess the outcome of the intervention, a structured questionnaire will be administered at baseline, midline (2 months after starting intervention) and end-line (4 months) as indicated the participants’ timeline in Fig. 2. During surveys, social demographic, knowledge and attitudes questions will be collected from all participating HCWs through an interviewer administered questionnaire. The questionnaires will be administered to the HCWs before the hand hygiene observations. In order to maintain systematic consistency for measurement indicators, the same research tools used at baseline will be used for mid-term, end-line and impact evaluation. In addition, observations of hand hygiene practice among the HCWs will be done at baseline, midline and end-line using an observation tool. Hand rinsates will be collected and analysed, and the results will be entered in a hand rinsates form. All the data collection tools to be employed will be guided by the WHO’s 5 moments for hand hygiene [37].

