### Strengths and limitations of the study

To the best of our knowledge, this may be the first study to evaluate the impact of environmental cues and mhealth on hand hygiene practice among HCWs. However, observations of hand hygiene practice among HCWs are likely to be affected by social desirability bias. To solve this challenge, RAs that will undertake the observations will be trained, standard WHO observation tools will be used, and where possible two observers will be used to observe hand hygiene behaviour simultaneously. In addition, our findings are likely to be influenced by a change in hand washing behaviour, which could be attributed to the recent COVID-19 pandemic. The effect of COVID-19 will be factored in during data analysis through stratification of data.

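### The protocol says health workers are masked to the intervention they receive, which the intervention makes impossible; social desirability in the observed primary outcome can therefore differ by arm

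*Protocol article*

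**What the plan says.** Under Delivery of the intervention, the paragraph on randomization and trial arms says that research assistants enrol the HCWs and that "they will be masked off the intervention they are receiving". The next paragraph, on masking, states: "The data analysts and the data collectors will be blinded to the group assignment". It gives the means for collectors: "independent teams will collect data from either arm of the trial", with separate training. HCWs do not appear in that paragraph.

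The same section describes what intervention HCWs get beyond the facilities, supplies and demonstration common to both arms. On messages, for the SMS option: "We shall configure the system to automatically send mhealth messages to HCWs at specific weekly intervals". On content: "the messages will also have educational jokes and response prompts where HCWs with the highest number of responses will win hand hygiene supplies". The section on stakeholders' workshops adds cues such as paint, pictures or branded mirrors at hand hygiene stations, with the final choice left to the workshop. Evaluation says that the midline process evaluation will establish "how many HCWs will be responding to the mhealth intervention as well as the aspects of the intervention that participants will have liked". It also places the interviewer-administered questionnaire before the hand hygiene observations.

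Strengths and limitations concedes that "observations of hand hygiene practice among HCWs are likely to be affected by social desirability bias". It answers with trained observers, WHO tools and, where possible, two observers at once.

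**The concern.** The masking sentence asserts something that the design cannot deliver, and it bears on the outcome most exposed to the lack of it. The primary outcome is the proportion of observed opportunities at which an HCW cleans the hands, recorded by someone standing on the ward. HCWs who have been told for weeks when and how to do this, and rewarded for replying, have more reason than controls to perform while watched. Such a reaction would look like an intervention effect even if unobserved practice had not changed. A reader who believes that participants were masked would wrongly set this explanation aside. The limitations section treats social desirability as a general problem, and a bias equal in both arms would largely cancel in the comparison. The part that differs by arm does not cancel.

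**Working it through.** No figure in the protocol depends on the masking statement, so the main check sets the sections side by side.

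1. **Who is meant.** The sentence names research assistants and HCWs before the pronoun. Only HCWs receive an intervention, so the claim is about them.

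2. **Can it be true in the intervention arm?** Messages go to the HCW's own phone, replies are invited and rewarded, and cues stand where hands are cleaned. The midline evaluation asks what was liked, which presumes that HCWs know what they received. Leaving the channel (SMS or WhatsApp) and the form of the cues to the workshop changes none of this.

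3. **Can it be true in the control arm?** In part. Control HCWs also get facilities, supplies and a demonstration, and might not know what the other arm gets. That is unawareness of the comparison, which the sentence does not say.

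4. **Does the masking paragraph agree?** No. It lists analysts and data collectors only.

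5. **Do the stated safeguards reach the problem?** Training, WHO tools and a second observer improve how behaviour is recorded. Outcome measurement adds that observers stand as unobtrusively as they can, 5 to 10 m away. That may lessen reactivity, but HCWs have consented, answer a questionnaire before observation and give a hand rinse immediately after it, so they can hardly be unaware of it. Blinding the collectors, even if it succeeds, does not change what the HCW knows.

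6. **Does the order of questions matter?** The questionnaire precedes observation. The article does not say whether the midline questions on exposure and liking are part of it. If they are, intervention HCWs are reminded of the intervention just before being watched, and controls have no counterpart.

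7. **Laboratory step.** *E. coli* colonies "will be identified by their dark blue to violet colour, and they will be counted and recorded per 100 ml of sample". Identification by colour involves judgement. The article does not say whether samples are coded or readers masked.

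**Illustration of size (the bias is an assumption).** Suppose being watched raises use by 5 to 10 percentage points more in the intervention arm. The sample size paragraph plans a 20% difference, from increases of 25% and 5% on a control proportion of 0.747, without saying whether these are absolute or relative.
- Absolute: 25 − 5 = 20 points; 5/20 = 25% and 10/20 = 50% of the planned difference.
- Relative: 0.747 × 1.25 = 0.934; 0.747 × 1.05 = 0.784; difference about 14.9 points; 5/14.9 = 34% and 10/14.9 = 67%.

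**The case against.** The best defence is that the sentence is loose wording for something reasonable: HCWs are not told the hypothesis or what the other arm gets. A subtle cue might also pass unnoticed as a trial intervention. This is possible, but it is not what is written. It cannot cover text messages, and HCWs are to be told the study's purpose at recruitment, after clusters are assigned. The authors do name social desirability openly, and that deserves credit; what is missing is that it can differ by arm.

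Several stronger readings are tempting but not supported:

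- *That plate reading is the only step that could be masked.* The protocol already blinds the analysts, and baseline observation made before delivery starts could be masked too.
- *That unmasked plate reading is an error.* No text says that readers know the arm. The term data collectors is undefined and might include them, and a condensed article may leave sample coding to the full protocol. Coding is a recommendation only.
- *That masked* E. coli *counts would be an unbiased check, so benefit should be claimed only if they agree.* Rinsates are taken straight after observation, so hands cleaned because someone was watching carry into the sample. Such a condition would also make a secondary outcome a gate for the primary claim, although the sample size rests on hand hygiene practice alone.
- *That both arms' samples should share laboratory batches.* Analysis within 4 hours and separate teams per arm make that a real logistic burden.
- *That exposure should be taken from message logs.* Delivery and response tracking is already planned for the SMS option.

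**Conclusion.** The point holds for the masking sentence and its consequence. The protocol claims that HCWs are masked to what they receive. Its own description of the intervention makes this impossible for the 225 HCWs planned in the intervention arm, and its masking paragraph does not repeat the claim. Because the primary outcome is directly observed behaviour, the estimated effect can contain an arm-dependent reaction to being watched, which the listed remedies do not address. How large that is cannot be learned from the documents; the 5 to 10 points used above, and so the shares of the planned effect, are illustrative. A reader might infer that the trial is invalid, or that the laboratory outcome rescues it. Neither follows. Lack of participant masking is inherent in this kind of intervention, and the need is to say so and to interpret the result accordingly. Absence of a statement on laboratory masking is an omission, not a contradiction.

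**What to change.** 1. Replace the sentence in the randomization paragraph with a statement that HCWs are not masked to the intervention. If something narrower is meant, such as not describing the other arm to them, state that instead. Make the masking paragraph agree.
2. In the limitations, name arm-dependent social desirability as a limit on the primary result, and say that observer training, tools and dual observation do not remove it.
3. In each survey round, ask any question about messages, cues or what was liked after that round's observation and any rinsate. The remaining questionnaire items can stay where they are.
4. As a cheap improvement, label rinsate bottles with arm-neutral codes so that plates are read without knowledge of facility or arm. Say plainly that this removes reader bias only, and treat *E. coli* as supporting evidence, not as a condition for claiming benefit.

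The cost is protocol wording, a change in question order and a coded label sheet held away from the plate readers; no extra samples are needed. The downside is a weaker stated blinding, which is the accurate one.

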### Outcome measurement

The primary outcome will be the proportion of utilized hand hygiene opportunities (number of critical times hand hygiene is observed to be done with soap and water or ABHR) out of the total number of observed hand hygiene opportunities. The secondary outcome will be *E. coli* concentration levels in hand rinsates from HCWs, which indicates recent fecal contamination and hand hygiene failure.

We shall determine the two outcome variables using two approaches. Firstly, observations based on the WHO’s 5 moments for hand hygiene which include: before touching a patient; immediately before performing an aseptic procedure; immediately after an exposure risk to body fluids (and after glove removal); after touching a patient and his or her immediate surroundings when leaving as well as after touching any object or furniture in the patient’s immediate surroundings, when leaving - even without touching the patient [37]. Hand hygiene observations will be conducted during the baseline, midline and end-line surveys. The hand hygiene observations will be done in the mornings (8 am – 12 pm) and evenings (4 pm – 8 pm) since these are considered to be peak treatment hours [36]. Within the targeted time, 20 hand hygiene opportunities will be observed for each of the selected HCWs (corresponding to 10 patients each with 2 hand hygiene opportunities, which will include before touching a patient and after touching a patient), and the used and missed opportunities will be recorded. Therefore, a total of 9000 hand hygiene opportunities will be observed by experienced researchers (HCWs or environmental health officers), who will observe from the least obtrusive point within a radius of 5–10 m of the patient wards [38].

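### With one separately trained observer team per arm, team and arm cannot be told apart in the observer-scored primary outcome, and observers are not blinded

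*Protocol article*

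**What the plan says.** In the protocol article, under Delivery of the intervention, item iv (Masking/blinding), the claim is: "The data analysts and the data collectors will be blinded to the group assignment". The means for the collectors is given next: "In order to achieve blinding for the data collection team, independent teams will collect data from either arm of the trial". Then: "In addition, data collectors will be trained separately".

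Under Outcome measurement: "The primary outcome will be the proportion of utilized hand hygiene opportunities". The observers record each opportunity as used or missed, and it is they "who will observe from the least obtrusive point within a radius of 5–10 m of the patient wards". On timing: "Hand hygiene observations will be conducted during the baseline, midline and end-line surveys".

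The cues are placed in intervention facilities only. The section on the stakeholders' workshops gives examples: "colours or pictures to paint around hand hygiene stations, branding of mirrors etc". The final choice is left to the workshop.

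Under Data analysis, item ii, the effect is estimated by logistic regression in a GEE framework with exchangeable correlation. The text names no observer or team term and no baseline or arm-by-time term. Table 3 lists percentage change in used opportunities as an indicator.

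Under Strengths and limitations, the safeguards against social desirability bias are observer training, standard WHO tools and, further, "where possible two observers will be used to observe hand hygiene behaviour simultaneously".

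**The concern.** Whether an opportunity arose and whether it was met is a judgement made at a distance on a busy ward, and it depends on how the observer was taught to score. If one team scores only intervention facilities and the other only control facilities, a more lenient team and an effective intervention look the same in the end-line data. Separate training takes away the main safeguard that would keep the two teams alike.

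A later analysis plan cannot fully repair this, because no observer's scores would exist in both arms. Adding facilities or opportunities does not help either. The bias stays the same size while the standard error shrinks, so a false positive becomes more likely.

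The rule is justified only as blinding. If it does not blind, the confounding is accepted for no return. A team or observer code in the dataset would also show the arm to analysts who are meant to be blinded.

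**Working it through.** **Is any observer in both arms?** The masking item assigns collectors by arm and separates their training. The Evaluation section keeps the same tools across rounds. The quality assurance section provides experienced assistants, pre-testing and a quality control team. The limitations section offers paired observers where possible. None of these places an observer in both arms or checks agreement between the teams. Two observers within one team can agree perfectly and still differ from the other team.

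**Does the rule blind?** Observers work at the wards, and cues such as paint or branding at hand hygiene stations would be there to see. A team that visits one arm may not know how the other arm differs, but that is not the same as being unaware of assignment.

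**Size in an end-line comparison.** The plan states no figure on this point, so there is nothing to reproduce. The inputs, from the sample size paragraph and Outcome measurement, are: control proportion 0.747, 225 workers per arm, 15 facilities per arm, 15 workers per facility, design effect 2.0, two-sided z of 1.96, and 20 opportunities per worker (450 × 20 = 9000). I take the 20 as applying to one round. The size of the team difference, d, is an assumption.

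Worker level:
- Effective n per arm = 225 / 2 = 112.5.
- SE = √(2 × 0.747 × 0.253 / 112.5) = 0.058, or 5.8 points.

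Opportunity level:
- ICC implied by the design effect = (2 − 1) / (15 − 1) = 0.071.
- Opportunities per facility = 15 × 20 = 300; per arm = 225 × 20 = 4500.
- Design effect = 1 + 299 × 0.0714 = 22.4; effective n = 4500 / 22.4 = about 201.
- SE = √(2 × 0.747 × 0.253 / 201) = 0.043, or 4.3 points.

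With no true effect, the chance of a significant result is Φ(d/SE − 1.96) + Φ(−d/SE − 1.96):

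| Assumed team difference | SE 5.8 | SE 4.3 |
|---|---|---|
| 0 points | 5% | 5% |
| 3 points | 8% | 11% |
| 5 points | 14% | 21% |
| 10 points | 41% | 64% |
| 15 points | 74% | 93% |

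The opportunity-level column depends on the ICC. For d = 5 it runs from 54% at an ICC of 0.02 (SE 2.4) to 17% at 0.10 (SE 5.1).

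**Effect of a baseline comparison.** I simulated 15 against 15 facility proportions with no true effect, 300 opportunities per facility and ICC 0.071, analysed by two-sided t-test. The true proportion of 0.5 and the baseline to end-line cluster correlation of 0.5 are assumptions.

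| Team difference at baseline → end-line | End-line only | Change from baseline |
|---|---|---|
| 0 → 0 | 4% | 5% |
| 5 → 5 | 17% | 6% |
| 10 → 10 | 49% | 5% |
| 0 → 5 | 17% | 16% |
| 0 → 10 | 48% | 47% |
| 5 → 15 | 84% | 47% |

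A constant difference cancels. A difference that arises or grows after baseline does not.

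**The case against.** The best reply is that the trial observes baseline, midline and end-line with the same tools, and that Table 3 names percentage change as an indicator. If each team scores consistently, comparing change removes its leniency. That is correct, and it limits the point. A reader might infer that every scoring difference must appear as intervention effect and that no analysis could help; the documents do not support that. What remains is that the GEE description does not fix a baseline-adjusted contrast, and that drift or expectation arising after baseline would survive one. Such a shift is plausible because the cues appear only after baseline.

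A second reply is that standard WHO tools, training, paired observers and a quality control team limit idiosyncratic scoring. They do, but nothing states that they calibrate one team against the other.

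A third is that the wording on teams is loose. Taken with separate training, however, one team per arm is the natural reading.

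A reader might also extend the criticism to the *E. coli* outcome. The text does not establish this. Rinsates are collected by a team that is not said to be split by arm, duplicates are taken, and colonies are counted in the laboratory.

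**Conclusion.** The concern holds in this limited form. Observer team is fully confounded with arm for the primary outcome. An end-line comparison carries the whole between-team difference, and a change comparison carries whatever part of it arises after baseline. The rule does not achieve its stated purpose, since the cues are likely to reveal assignment to anyone observing on the ward.

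With the plan's own inputs and no true effect, team differences of 5 and 10 points would raise the nominal 5% error at end-line to about 14% and 41%, or to 21% and 64% with opportunity-level data at an ICC of about 0.07. These are illustrations. The documents give no between-team figure, the true difference could be smaller, and the percentages apply where the difference is not removed by baseline adjustment. The confounding itself does not depend on these assumptions. It follows from the allocation of teams.

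**What to change.** Replace the rule in the masking item:

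- Train all observers together to one scoring standard.
- Rotate each observer across intervention and control facilities in every round, on a balanced rota.
- Record observer identity and include observer in the model.
- State that arms are compared with adjustment for baseline.
- Do not tell observers the allocation, and drop the claim that separate teams achieve blinding. Analyst blinding can stay.
- State whether rinsate collectors are split by arm. If they are, put them on the same rota.

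The cost is protocol wording, a rota, and some extra travel and scheduling. The documents give no staffing figures, so the travel cannot be sized. The drawback is that observers who see both arms may guess allocation more easily, but visible cues already allow that. At publication the formative phase was under way and the intervention had not begun, so the change could be made before outcome data were collected. Once the rounds have been observed by separate teams, it cannot be recovered.
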